## Abstract

**Introduction:**

A Low Glycaemic Index (LGI) diet is a proposed lifestyle intervention in non-alcoholic fatty liver diseases (NAFLD) which is designed to reduce circulating blood glucose levels, hepatic glucose influx, insulin resistance and de novo lipogenesis. A significant reduction in liver fat content through following a 1-week LGI diet has been reported in healthy volunteers. Changes in dietary fat and carbohydrates have also been shown to alter gut microbiota composition and lead to hepatic steatosis through the gut-liver axis. There are no available trials examining the effects of an LGI diet on liver fat accumulation in patients with NAFLD; nor has the impact of consuming an LGI diet on gut microbiota composition been studied in this population. The aim of this trial is to investigate the effects of LGI diet consumption on liver fat content and its effects on gut microbiota composition in participants with NAFLD compared with a High Glycaemic Index (HGI) control diet.

**Methods and analysis:**

A 2×2 cross-over randomised mechanistic dietary trial will allocate 16 participants with NAFLD to a 2-week either HGI or LGI diet followed by a 4-week wash-out period and then the LGI or HGI diet, alternative to that followed in the first 2 weeks. Baseline and postintervention (four visits) outcome measures will be collected to assess liver fat content (using MRI/S and controlled attenuation parameter-FibroScan), gut microbiota composition (using 16S RNA analysis) and blood biomarkers including glycaemic, insulinaemic, liver, lipid and haematological profiles, gut hormones levels and short-chain fatty acids.

**Ethics and dissemination:**

Study protocol has been approved by the ethics committees of The University of Nottingham and East Midlands Nottingham-2 Research Ethics Committee (REC reference 19/EM/0291). Data from this trial will be used as part of a Philosophy Doctorate thesis. Publications will be in peer-reviewed journals.

**Trial registration number:**

NCT04415632.

Strengths and limitations of this studyA carefully controlled human Low Glycaemic Index diet intervention to reduce liver fat in non-alcoholic fatty liver diseases (NAFLD) using cross-over study deign.The first NAFLD patient study that explores the mechanistic effects of dietary glycaemic index on liver fat accumulation using advanced MR protocols.Uses the controlled attenuation parameter as a biomarker to evaluate efficacy of diet intervention.Findings from small sample size may not be generalisable to all patients with NAFLD so will require replication in larger long-term randomised controlled trial.The 2-week time frame of the intervention, especially in light of isoenergetic diet, may not be sufficient to observe significant changes in liver fat.

## Introduction

Non-alcoholic fatty liver disease (NAFLD) is a growing global health concern increasing in parallel with the worsening epidemics of obesity and diabetes.^1 2^ Recent reviews indicated that one billion people worldwide have NAFLD (estimated prevalence 25.4%).^3^ NAFLD is characterised by the fat accumulation in hepatocytes exceeding 5% of liver weight and encompasses a spectrum of disease severities. Common clinical risk factors that are highly associated with NAFLD include obesity, insulin resistance, type 2 diabetes and metabolic syndrome.^3 4^ NAFLD is recognised as the hepatic manifestation of metabolic syndrome.^5–7^

Western dietary habits occurring concurrently with a sedentary lifestyle and genetic factors are associated with insulin resistance, adipocyte proliferation and gut microbiota alteration which may be implicated in NAFLD.^8^ Dietary habits, hormones secreted from the adipose tissue, gut microbiota composition and genetic factors are all implicated in the pathogenesis.

To date, there are no drugs with regulatory approval for treating NAFLD, and lifestyle changes including modification of dietary patterns together with increased physical activity is the initial step to treat this disease.^9^ Dietary approaches beneficial in NAFLD management include reductions in saturated and trans fatty acids, total carbohydrates and animal-based protein intake and increases in the intake of polyunsaturated fatty acids, monounsaturated fatty acids, plant-based proteins and antioxidants.^4^ Furthermore, evidence from a systematic review and meta-analysis of randomised controlled trials (RCTs) on patients with NAFLD has shown that lifestyle-induced weight loss of ≥7% improved histological disease activity, as well as cardiometabolic risk profile, in less than 50% of the study population (n=373 patients).^10^ A recent systematic review has concluded that despite the abundance of interventional studies on dietary management in NAFLD, there is still a lack of evidence-based specific recommendations, other than that weight loss may benefit some; and few studies have measured liver-related outcomes.^11^ Moreover, the dietary effects on liver-related outcomes that are mediated by gut microbiome have not been studied in these patients.^12^

More recently, the Glycaemic Index (GI) and glycaemic load (GL), of diet; has been proposed as an important predictor of NAFLD progression.^4 13^ The GI of a food ranks the glycaemic response under conditions in which the quantity of carbohydrate is controlled,^14 15^ whereas the GL additionally considers portion size.^16^

NAFLD patients have been found to consume a diet high in High GI (HGI) foods^4^ which are correlated with insulin resistance, metabolic dysfunction,^4^ and liver dysfunction.^17^ In addition, HGI dietary habits have been significantly associated with high-grade liver steatosis in patients with insulin resistance^18^ while limiting HGI foods is beneficial in NAFLD.^19 20^ Further, previous pilot study showed that only 1 week of consuming HGI diet caused significant increase in hepatic stores of fat when compared with isocaloric Low GI (LGI) diet consumption.^21^ A recent review concluded that both low GI and GL diets resulted in significant reductions in hepatic fat mass in a cohort of 269 participants.^16^ However, these effects were not attributed to the LGI diet alone and were confounded with other lifestyle interventions.^16^

Evidence from animal and human studies also showed that diet is the most important modifying factor in the development of human gut microbiome.^22–24^ Dietary alterations can rapidly change the human gut microbiota composition in relatively short time periods^25–27^ and in as little as 24 hours.^28–30^ Certain dietary factors which modify gut microbiota have been associated with a number of diseases including obesity^31^ metabolic syndrome,^22 32 33^ type 2 diabetes,^34^ immunological dysfunctions.^35^ Such dysbiosis in diet-induced NAFLD has been shown to stimulate hepatic fat disposition and promote NAFLD progression to non-alcoholic steatohepatitis (NASH).^36 37^ This is suggested to be mediated by modulation of gut permeability, dietary choline metabolism, bile acid metabolism, endogenous ethanol production and immune balance.^36 37^ Gut microbiota modulated by diet can increase the energy extraction from the breakdown of non-absorbable polysaccharides with the production of monosaccharides and short chain fatty acids (SCFAs) which are substrates for hepatic de novo lipogenesis and carbohydrate biosynthesis.^38^ Certain SCFAs have also been implicated in improving glucose and lipid metabolism beneficial to the host.^39^ Therefore, there is a potential to modulate gut microbiota through dietary changes as a means of NAFLD prevention or alleviation.^11 40^

We describe here our study protocol designed to assess the effects of a specific defined GI dietary manipulation^21^ on liver fat content and its effects on gut microbiota composition in participants with NAFLD compared with a higher GI diet as a control diet. The diets will be adjusted to each participant to meet their energy requirements and the macronutrient composition of the diets will be carefully controlled ensuring that differences in GL are due to differences in GI.

## Objectives

### Primary objective

1. To investigate the effects of defined LGI versus HGI diet on liver fat accumulation in participants with NAFLD following a 2-week intervention period while controlling for the energy consumption and amount of carbohydrate intake.

### Secondary objectives

To investigate the effects of LGI versus HGI diet on gut microbiota composition and its correlations with liver outcomes in participants with NAFLD following a 2-week intervention period.To investigate the changes in blood metabolic biomarkers (glycaemic, insulinaemic, liver, lipid, haematological profiles, gut hormones and plasma SCFAs) between LGI and HGI diet groups following a 2-week intervention in participants with NAFLD.To evaluate controlled attenuation parameter (CAP) as a tool to test the efficacy of a dietary intervention by comparing its performance characteristics with that of MR Spectroscopy (MRS) as a gold standard.To validate the European Prospective Investigation of Cancer Food Frequency Questionnaire (EPIC-FFQ) in Nottingham NAFLD patients against food diary.

## Methods and analysis

### Trial design

This is a randomised 2×2 cross-over mechanistic trial including two arms, each of 2 weeks duration comparing an LGI diet and a control HGI diet based on that defined by Bawden *et al*
21 and Morgan *et al*.^41^ The study design is illustrated in figure 1.

**Figure 1 F1:**
[figure not shown]
Schematic diagram for cross-over trial of LGI diet versus HGI diet effects on liver fat content in participants with NAFLD. FFQ, Food Frequency Questionnaire; HGI, High Glycaemic Index; IPAQ, International Physical Activity Questionnaire; LGI, Low Glycaemic Index; NAFLD, non-alcoholic fatty liver diseases.

### Public and patient involvement

We collaborated with the National Institute of Health Research (NIHR) Nottingham Biomedical Research Centre (BRC) patient advisory group, and we met seven patients who were interested in study participation. They expressed strong support for the research objectives and the recent meeting the group considered the 2-week cross-over intervention feasible and acceptable. Patient feedback informed the participant recruitment through information content and delivery methods. They also assisted in the study design to enhance participant compliance and commitment to the diet.

### Participants and recruitment

We aim to recruit 16 participants with NAFLD to complete both phases of 2×2 cross-over trial. The initial screening criteria for inclusion is a CAP score of >288 dB/m; this value correlates with MRI- Proton Density Fat Fraction (PDFF) estimation of >5% fat of liver weight which indicates that they have a fatty liver.^42^

NAFLD patients will be recruited either from the existing database of ‘The Scarred Liver Project’ in the UK who have given consent to be contacted to participate in future research (approved by East Midlands-Leicester Research ethics committee ref: B/EM/0123) or from liver clinics at the Nottingham University Hospitals NHS Trust who had a FibroScan with CAP or participants from public (advert in local and social media). The eligibility criteria are summarised in box 1. All participants will provide a written informed consent by trained research team before they enter the trial. Potential participants will be free to withdraw at any time. In the event of their withdrawal, it will be explained that their data collected so far cannot be erased and we will seek consent to use the data in the final analyses where appropriate. In the event of a participant withdrawing or being unable to continue the intervention periods after randomisation, a replacement will be recruited who will be assigned to the same diet group to ensure a 1:1 ratio for the two diet groups. We will continue recruiting until 16 participants have fully completed the study.

Box 1Eligibility criteriaInclusion criteriaAdult males and females aged from 18 to 65 years (balanced number).Detected non-alcoholic fatty liver diseases (NAFLD) by controlled attenuation parameter (CAP)-FibroScan >288 dB/m or by MRI-proton density fat fraction >5% fat of liver weight.Body mass index ≥25 kg/m^2^.Abdominal obesity (waist circumference >102 cm for males and >88 cm for females).Have current moderate to high Glycaemic Index diet intake of ≥60 (Assessed from a completed 7-day day food diary).Available to give informed consent.Available to undergo MRI/spectroscopy and CAP-FibroScan.Exclusion criteriaCurrent smokers and excessive alcohol drinkers (>14 units/week).Perimenopausal (irregular periods) women.Participants with other liver abnormalities.Participants with history of gastrointestinal surgeries, depression, eating disorders or difficulties.Participants using pharmacological agents for obesity or NAFLD.Participants with type 1 diabetes.Participants with type 2 diabetes on second line medications (eg, glucagon-like peptide-1 analogues).Participation in any other trial in the last 3 months.Participants on any special diets (eg, vegetarians).Intolerance to foods included in the diet plan.

### Screening process

Participants will be invited to attend an initial screening visit (figure 1). At this visit, participants will be consented and asked to complete a prescreening questionnaire (including taking height, weight and blood pressure measurements) to establish whether they meet the study criteria. Participants will be asked to fill out a 7-day food record and post it after 1 week of their initial screening visit. This is to avoid giving patients with NAFLD, who might be at risk of developing diabetes, a much higher HGI diet than they habitually consume. Using 7-day food records, we will characterise the baseline habitual GI diet intake of all potential volunteers at screening period. Participants also will be required to complete a FFQ for validation against the 7-day food records. We will use EPIC-FFQ that was validated for use in Norfolk cohort.^43^ After completion, participant’s eligibility will be reassessed based on analysis of diet information using Nutritics software (Nutritics, Dublin, Ireland, 2018). Those with a habitual LGI diet intake (GI <60) will be excluded from the study. Only patients who have a moderate to HGI diet intake (GI ≥60) will be invited to attend the next screening preparation visit.

Then at next screening visit (visit 2), the participants will be asked to fill out International Physical Activity Questionnaire (IPAQ).^44^ A trained dietitian will instruct participants on how to measure study food provided using measuring jug and spoons and how to fill in study diet compliance sheets. They will be instructed on stool collection and preintervention visits requirements. Participants will be asked to avoid eating probiotics and/or prebiotics supplements or drinks for 1 week before the intervention period (standardisation week). All instructions will be provided to each participant in a form of Home Guide Booklet.

Each eligible participant will be assigned randomly to undergo either HGI diet (HGI group) or LGI group first and then crossover to either HGI or LGI diets.

### Randomisation and blinding

Enrolled participants who meet the eligibility criteria will be randomised to one of two groups which will dictate the order in which they receive the LGI or HGI diet. They will then receive the second diet depending on which diet they have first received. The random allocation sequence (AB or BA) will be generated by one of the trial co-ordinators; who will have no contact with the participants, using block randomisation by impartial biostatistics. The online randomisation package (http://randomization.com) will be used to allocate the sequences of the diet groups to the participants in equal numbers. Once the random number is generated, both trial investigators and participants are aware of the diet sequence (ie, whether the participant is going to start with LGI diet; A or HGI diet; B). The diets then will be delivered to the participant according to the sequence. The trial outcome measures will be determined by blinded researcher using codes on samples that will be sent for 16S ribosomal RNA (rRNA), blood marker and MRI/CAP-FibroScan analyses. The blinded allocation will be provided to the study statistician at the end of the study and once the analysis has been completed, the study statistician will be provided with the unblinded allocation.

### Study protocol

Following the screening phase and standardisation week, each participant will experience two, 2-week intervention phases, with a 4-week washout period between interventions. Before and after each intervention period they will attend the Imaging Centre (Sir Peter Mansfield Imaging Centre) for MRI scan measurements and then will attend the Biomedical Research Centre for FibroScan, and blood and stool samples collection. During each intervention phase each participant will be required to consume all the food that has been provided, fill in dietary compliance sheets and complete Visual Analogue Scales (VAS) relating to subjective appetite ratings.

### Design of the dietary interventions

Energy expenditure will be estimated for each participant using the individual’s basal metabolic rate calculated from Henry-modified Schofield formula^45^ and multiplied by an activity factor based on the IPAQ score physical activity levels. A menu, consisting of meals for 3 days personalised for energy requirement, will be devised (these meals are repeated over 2 weeks) by adjusting a template according to their estimated energy requirement in order to minimise weight change during the intervention phase. The diet consists of normal food closely resembling that described by Bawden *et al* study.^21^ A diet template of 2000 kcal/day with energy proportions distributed as 55% from carbohydrates, 15% from protein and 30% from fat^46^ are designed and food quantities will be modified to supply the energy requirements for each participant. Three-day cycle menu plans are designed for each diet (LGI/ HGI). Table 1 shows example template menus for both HGI (a) and LGI (b) diets.

**Table 1 T1:** Illustration of HGI (A) and LGI (B) diet templates for use in the study

	Weight (g)	Energy (kcal)	Carbohydrates (g)	Protein (g)	Fat (g)	Fibre (g)	GI	GL
HGI diet sample (A)								
Breakfast								
Sultana Bran Cereal	90	268	58	6.6	1.3	10.1	90	52.2
Skimmed milk	180	63	8.3	6.3	0.54	0	48	4
Roasted peanuts	15	90	2.3	3.7	7.4	1.3	14	0.32
Glucose	10	40	10	0	0	0	100	10
Water	170	0	0	0	0	0	0	0
Meal total		461	78	16.6	9.2	11.4	85.3	66.5
Lunch								
Margarine	25	102	0.13	0.05	11.3	0	0	0
Fruit loaf	144	395	76	11.4	5.2	4.6	90	68.4
Roasted turkey slice	42	47	0.67	10	0.5	0.12	0	0
Cheddar cheese slice	25	104	0.03	6.4	8.7	0	0	0
Strawberry yoghurt	125	88	16.3	5.6	0	0.38	85	13.855
Meal total		735	93	33.4	25.7	5.1	88.44	82.255
Dinner								
Cottage pie (ready meal)	400	441	44	18	21.6	4.8	66	29.04
Low fat strawberry yoghurt	125	88	16.3	5.6	0	0.38	85	13.855
Water	170	0	0	0	0	0	0	0
Glucose	10	40	10	0	0	0	100	10
Mars bar	58	237	37	2.4	8.9	0.87	65	24.05
Meal total		806	107	26	30.5	6	72.69	76.954
Menu total		2002 Kcal	278 g (55.5%)	76 g (15.2%)	65 g (29.3%)	22 g	82.1	225.706
LGI diet sample (B)								
Breakfast								
All Bran cereal	90	239	42	11.2	3.1	22.1	43	18.06
Semi-skimmed milk	160	76	7.2	5.6	2.7	0	25	1.8
Orange juice	250	96	22	1.5	0.25	0	53	11.66
Meal total		410	71	18.2	6	22.1	44.39	31.52
Lunch								
Pumpernickel bread	180	408	74	15.7	5.6	11.7	41	30.34
Black cherry yoghurt	150	209	24.2	4.8	10.4	0.75	17	4.114
Soft cheese	51	129	1.5	2.7	12.4	0	34	0.51
Meal total		745	99	23.2	28.4	12.5	35.32	34.96
Dinner								
Lasagne (ready meal)	290	413	42	21.5	17.7	4.9	36	15.12
Apple	174	92	20	1	0.87	2.1	38	7.6
Semi-skimmed milk	150	71	6.8	5.3	2.6	0	25	1.7
Fruit and nuts mix	60	267	24.6	8.4	15	3.9	15	3.69
Meal total		843	93	36.2	36.1	10.9	30.22	28.11
Menu total		1999 kcal	264 g (52.7%)	78 g (15.5%)	71 g (31.8%)	46 g	36.64	94.594

GI, Glycaemic Index; GL, glycaemic load; HGI, High Glycaemic Index; LGI, Low Glycaemic Index.

The GI values of commercial food items are generated from that reported by Henry *et al*,^47^ as well as Nutritics software databases (Nutritics). The dietary GI of the menu is calculated from GI proportional contribution to total carbohydrate using the equation: GI=∑(C_food_/C_total_) × GI_food_; where C_food_ is the amount of carbohydrate contained in each digested food (g), C_total_ is the total carbohydrate in the meal and is the reported GI of the food.^21^ The GL of the diet is calculated based on the dietary GI and the amount of carbohydrate provided (the same in both diets) using the following equation: GL=(GI_food_ × C_food_)/100; where GI is the GI of each digested food and food is the amount of carbohydrate in the food.^21^ Food composition analysis and evaluation were performed using Nutritics software (Nutritics, Dublin, Ireland, 2018).

Participants will be provided with the food at the start of each 2-week diet period and will be clearly instructed on safe food storage and reheating. They will be required to complete dietary compliance sheet on a daily basis. Instructions on dietary compliance will be given at each study period and the dietary compliance records will be reviewed regularly during the intervention to assess their compliance. For the first 1 week prior to the intervention (1-week standardisation), and during the 4-week wash-out period, participants will be asked to avoid eating probiotics, yoghurt and cultured milk drink; if any, to standardise their gut microbiota and avoid any carry-over effects as shown in previous studies.^48 49^ Meal-timing will be standardised among all participants as much as possible during the intervention as well as during the standardisation period.

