## Discussion and research implications

Building on previous findings from Morgan *et al*
41 and Bawden *et al*,^21^ this study will investigate the effects of LGI versus HGI diets in participants diagnosed with NAFLD, over a 2-week period. While previous studies showed a significant impact of LGI on liver fat reduction and other metabolic biomarkers, questions remain on the effect in individuals with NAFLD and the longer-term impact. Due to the carefully controlled nature of the intervention, the sample size can be reduced, and the research used to probe more specifically into the direct effects of varying the type of carbohydrate intake. Many studies have shown that energy reduction has a profound effect on liver fat and metabolic health,^68^ but these diets have been found to be unsustainable in a community setting.^10^ Proof of the direct impact of varying a specific characteristic of one macronutrient without reducing the overall intake of the macronutrient consumed, or the overall energy consumed would provide a strong basis for further investigations on the sustainability of such diets.

This study takes advantage of advanced MR protocols which provide a powerful method for non-invasively assessing the effects of lifestyle interventions on metabolic health alongside other physiological measures. Biopsy measurements are uncomfortable for the patient carrying a number of significant risks and would be ethically inappropriate in otherwise healthy individuals. In addition, biopsy only provides a small sample from one region of the liver. MRI and MRS have been well validated^52 69^ and allows for repeated tissue specific measurements of fat fraction with minimal risk to study volunteers, thus enabling robust longitudinal studies on the impact of nutrition on metabolic health and liver disease. Additionally, recent research has highlighted the potential significance of lipid composition in metabolic disorders and novel methodologies for measuring this using MRI and MRS have been developed.^53^ These advanced techniques will be used to assess not only lipid accumulation but also the effect on saturated, unsaturated and polyunsaturated fat stores in the liver. Subcutaneous and visceral fat volumes will also be obtained alongside hepatic fat fraction during the scan session giving a more complete picture of abdominal lipid deposition.

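### The only template menus shown differ in carbohydrate (278 vs 264 g) and twofold in fibre (22 vs 46 g); unless the 3-day averages are close, an effect cannot be credited to GI alone

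*Protocol article*

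**What the plan says.** The primary objective compares the two diets "while controlling for the energy consumption and amount of carbohydrate intake". The last paragraph of the Introduction calls the study one "designed to assess the effects of a specific defined GI dietary manipulation" and promises that "the macronutrient composition of the diets will be carefully controlled ensuring that differences in GL are due to differences in GI". Under Design of the dietary interventions, the 2000 kcal template has "energy proportions distributed as 55% from carbohydrates, 15% from protein and 30% from fat", each diet runs on a 3-day menu cycle, and "Table 1 shows example template menus for both HGI (a) and LGI (b) diets". The text below the table bases GL on "the amount of carbohydrate provided (the same in both diets". The Discussion looks ahead to "Proof of the direct impact of varying a specific characteristic of one macronutrient without reducing the overall intake of the macronutrient consumed".

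Fibre is a printed column in Table 1, but the article gives no fibre target or matching rule. The limitations listed after the abstract and at the end of the Discussion concern sample size and the 2-week duration. Neither mentions fibre.

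**The concern.** There are two parts, of unequal weight.

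**Carbohydrate.** The text says the amount is equal, but the two printed menus do not have equal amounts, and the low-GI menu falls short of the 55% target. If carbohydrate differs, part of the GL difference comes from quantity and not from GI.

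**Fibre.** The low-GI menu has about twice the fibre of the high-GI menu. If that holds over the cycle, each participant changes fibre and GI at the same time. A cross-over removes differences between people, but not a second dietary feature that moves with the diet. Food quantities are scaled to energy need, which would scale fibre and GL together, so variation between participants does not help to separate them. Gut microbiota and plasma short-chain fatty acids are outcomes of the trial, and the Introduction itself describes a route from "non-absorbable polysaccharides with the production of monosaccharides and short chain fatty acids (SCFAs) which are substrates for hepatic de novo lipogenesis". On the protocol's own reasoning, fibre is then a rival explanation. At stake is the statement that an effect is due to GI.

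**Working it through.** **Inputs.** All come from Table 1: the food rows and the menu totals.

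**Step 1: reproduce the printed totals by summing the rows.**

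| Example day | Energy (kcal) | Carbohydrate (g) | Fat (g) | Fibre (g) | GL |
|---|---|---|---|---|---|
| High GI, printed | 2002 | 278 | 65 | 22 | 225.7 |
| High GI, row sum | 2003 | 279.0 | 65.4 | 22.55 | 225.7 |
| Low GI, printed | 1999 | 264 | 71 | 46 | 94.6 |
| Low GI, row sum | 2000 | 264.3 | 70.6 | 45.45 | 94.6 |

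The totals agree to about 1 g or 1 kcal, so the gaps are not adding-up errors.

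**Step 2: size of the carbohydrate gap.** 278 − 264 = 14 g, or 14/278 = 5.0%. The target is 0.55 × 2000/4 = 275 g. The high-GI day is 3 g above it and the low-GI day 11 g below.

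**Step 3: share of the GL contrast due to carbohydrate amount (midpoint split).**
- GL difference: 225.7 − 94.6 = 131.1.
- GL per gram of carbohydrate: 225.7/278 = 0.812 and 94.6/264 = 0.358.
- Part due to amount: 14 × (0.812 + 0.358)/2 = 8.2 units, and 8.2/131.1 = 6.2%. With row sums it is 6.6%.
- The remaining 94% or so is due to GI, so the Introduction's aim for GL is nearly met even on this day.

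**Step 4: size and source of the fibre gap.** As printed, 46 − 22 = 24 g, a ratio of 2.1. By row sums, 45.45 − 22.55 = 22.9 g. The cereals contribute 22.1 − 10.1 = 12.0 g and the breads 11.7 − 4.6 = 7.1 g. Together that is 19.1 of 22.9 g (83%).

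**Step 5: what the two unseen days could do.** Suppose the gap on each unseen day is f times the gap shown. The cycle-average gap is then the shown gap × (1 + 2f)/3. The range of f is an assumption, because the article does not show those days.

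| f | Fibre gap, low minus high GI (g/day) | Carbohydrate gap, high minus low GI (g/day) |
|---|---|---|
| −0.5 | 0 | 0 |
| 0 | 8 | 4.7 |
| 0.5 | 16 | 9.3 |
| 1 | 24 | 14 |
| 1.5 | 32 | 18.7 |

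Both gaps vanish at f = −0.5, but what that requires is very different. For carbohydrate, the low-GI diet needs 7 g more than the high-GI diet on each other day, which is plausible for menus built to a 55% target. For fibre, the low-GI diet needs 12 g less than the high-GI diet on each other day, which reverses the pattern shown. Even if fibre were identical on both unseen days, 8 g/day would remain.

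**The case against.** The strongest reply is that Table 1 is an illustration. The carbohydrate statement describes the diets, which are 3-day cycles adjusted to each person, and one day in three cannot show that a statement about a cycle is false. This stands for carbohydrate. The statement is untrue of the printed menus, but the cycle may still meet it, and the gap is small in any case.

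A second reply is that fibre matching was never promised. Only energy and carbohydrate amount are said to be controlled, the objectives compare a low-GI with a high-GI diet, and the diets follow earlier studies on purpose. This also stands. A reader might infer that the protocol breaks a commitment to match fibre, or that the primary comparison is confounded and invalid. The document supports neither: it makes no such commitment, and the difference between the two diets as delivered is estimated validly whatever carries it.

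A third reply is that the Discussion sentence is conditional, and that the same paragraph speaks of the type of carbohydrate, which could include fibre. Fermentation may even be part of how a low-GI diet works. That is a reason to state the claim more clearly. As worded, together with the Introduction, it points to one property, GI.

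Finally, a condensed article may leave full menu composition to the full protocol. The absence of the other two days is therefore not held against the plan, and the fibre point is conditional on them.

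**Conclusion.** The point holds in two parts. The equal-carbohydrate statement does not fit the only menus shown (14 g, 5%). This is minor, at about 6% of the GL contrast, and may cancel over the cycle. A reader might infer that it undermines the attribution of the GL difference to GI; the calculation shows that it does not.

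The fibre difference is the substantive part: 24 g on the example day, a factor of 2.1, with no stated target. Unless the cycle averages are close, the design cannot support a conclusion about GI alone, especially for microbiota and short-chain fatty acids. A reader might also infer that fibre would explain a fall in liver fat. The Introduction does not settle this: it names these acids as substrates for fat synthesis in the liver and also credits some of them with metabolic benefit, so the direction is open.

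The printed figures are certain. The consequence rests on the two unseen days. The trial remains valid, and the matter should be fixed because it limits what may be concluded.

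**What to change.** Take the steps in this order.

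1. Compute the 3-day cycle averages of carbohydrate, fat and fibre for each diet, with the nutrition software already in use.
2. Only if average carbohydrate differs, rebalance the low-GI cycle towards 55% of energy, or replace the statement of equality with the actual amounts. Adjusting the example day first could create a mismatch: if the other days already compensate, adding 11 g to that day puts the low-GI average 11/3 = 3.7 g above the high-GI average.
3. If average fibre differs, word the conclusion as a lower-GI, higher-fibre diet against a higher-GI, lower-fibre diet at equal energy. Narrow the Discussion sentence to match, and add fibre to the limitations.

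Fibre matching is not requested. It would mean changing mainly the cereal and the bread, could shrink the GI contrast, and would depart from the diets the trial follows. The cost is a recalculation and some wording, plus menu changes only if step 2 calls for them and that route is chosen. The price is a slightly narrower mechanistic claim. The test, the sample size and the whole-diet objective stay as they are.
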